# The effect of home-based low-volume, high-intensity interval training on cardiorespiratory fitness, body composition and cardiometabolic health in women of normal body mass and those with overweight or obesity: protocol for a randomized controlled trial

**DOI:** 10.1186/s13102-019-0152-6

**Published:** 2019-12-30

**Keywords:** High intensity low-volume interval training, Overweight, Obesity, Body composition, Cardiometabolic health, Physical activity, Exercise, Women

## Abstract

**Background:**

There is a high prevalence of women in South Africa with overweight and obesity which is associated with an increased risk of cardiometabolic disorders. Perceived barriers such as lack of time and motivation reduce engagement in beneficial activity behaviours for health. High-intensity interval training (HIIT) is a time-efficient and effective way to improve cardiometabolic risk profile regardless of a loss in body mass or change in body composition. This randomized controlled trial aims to determine the effects on cardiorespiratory fitness, body composition and cardiometabolic health and feasibility of a home-based 14-week HIIT program in women with overweight/obesity or normal body mass.

**Methods:**

One hundred and twenty women (18–40 years old) with a body mass index between 20 and 35 kg/m^2^, will be stratified according to their BMI (normal, BMI 20–24.9 kg/m^2^; or high BMI ≥25 kg/m^2^) and randomized into a HIIT exercising group (HIIT) or a non-exercising control group (CON). HIIT participants will perform exercises for 11 min/session six times per week for a period of 14 weeks. The 2 × 4 HIIT protocol will require a work phase of own-body weight exercise lasting 2 minutes (85% VO_2_peak), repeated four times and separated by a one-minute active rest phase (65% VO_2_peak). CON participants will be asked to maintain their normal habitual lifestyle. Outcomes of cardiorespiratory fitness, body composition, echocardiography, central blood pressure, arterial stiffness and biomarkers of cardiometabolic health will be measured before and after the 14-week intervention. Every 4 weeks during the intervention, an objective estimation of compliance to the study protocol will be assessed by measuring participant physical activity over 7 days using an Actigraph GT3X accelerometer.

**Discussion:**

Supervised laboratory-based HIIT interventions are effective in improving cardiometabolic health. More pragmatic exercise protocols may however show to be successful for mitigating barriers to the engagement in physical activity and exercise resulting in positive benefits to health. Investigation into home-based HIIT regimens are important in women, where globally the rising trend of overweight and obesity overshadows that of men. The results from this study may therefore inform future research on effective exercise prescription for women’s health.

**Trial registration:**

Pan African Clinical Trial Registry (www.pactr.org - id no: PACTR201806003434299), 6th June 2018.

## Background

Non-communicable diseases (NCDs), including overweight and obesity, are estimated to cause 71% of deaths worldwide and 51% of deaths in South Africa [1], a statistic which outnumbers those deaths caused by communicable diseases [2]. The most recent data from the South African National Health and Nutrition Examination Survey (SANHANES) reports that 64% of South African women older than 15 years, are overweight or obese (body mass index (BMI) > 25 kg/m^2^) and therefore at a greater risk of suffering from other NCDs [3]. These data are in line with global trends of obesity whereby more women than men are overweight and obese [4]. Excess weight gain or obesity is associated with concurrent increases in the incidence of hypertension, risk of type 2 diabetes, serum low density lipoprotein (LDL) cholesterol concentrations, and cardiovascular and metabolic disease risk [5, 6]. Obesity is also associated with several diseases in women including certain cancers (including breast and colon) [7–9], depression and sleep disturbances [10, 11], as well as all-cause mortality [12–14]. Hence it is not surprising that lifestyle interventions aimed at weight loss are still considered a cornerstone in the prevention and management of disease risk in women [15]. Following the World Health Assembly’s release of a comprehensive global monitoring framework and targets for prevention and control of NCDs [16], the South African National Department of Health (NDoH) also issued a five-year strategic plan for the prevention and control of NCDs between the years 2013–2017. The strategic plan aimed to achieve a 10% reduction in overweight and obesity, 20% reduction in elevated blood pressure and 10% increase in participation in physical activity (PA) [17] through lifestyle modifications by the year 2020 [18]. Public health strategies in South Africa have also emphasised increasing energy expenditure through an increase in daily PA and/or participation in exercise for maintaining ideal body mass. However, more research on engagement in and the effect of different possible exercise strategies on health outcomes is needed.

### Engagement in exercise and PA and barriers to participation in PA

Increasing participation in exercise and PA is associated with a decrease in body fat [19–22], which reduces one’s risk of obesity-related diseases [23, 24] and all-cause mortality [12, 14]. Current PA guidelines recommend that adults take part in at least 150 min of moderate intensity exercise or 75 min of vigorous intensity exercise per week for weight management [25]. However, only about 50% of healthy adults worldwide meet these recommended PA guidelines [3, 26]. Physical inactivity, which is defined as not meeting the recommended guidelines, is associated with hypertension, diabetes and obesity [27]. Lack of time [28], family responsibilities [29], fatigue or feelings of weakness, lack of motivation, confidence, self-discipline and unaffordable exercise programmes as well as not making exercise a priority and health issues are well-documented barriers to sufficient PA participation in healthy populations [29–32]. A survey of women aged 18–49 years, from low-income households in Latin America who were at risk of type 2 diabetes indicated that lack of willpower and energy were the most frequently perceived barriers to physical activity engagement [33]. In people with diagnosed obesity-related chronic diseases e.g. cardiovascular disease and type 2 diabetes, and who are referred to exercise-based rehabilitation programmes, independent engagement in exercise and physical activity behaviours remains low during the maintenance phases of rehabilitation [34–36]. Another well-established reason for poor engagement in long-term exercise maintenance programmes is due to lack of transport or the associated costs of transport to rehabilitation centres especially in lower income households [35]. Finally, women who are overweight or obese report that social influence and fear of injury are important barriers to exercise [33]. More research is therefore warranted to investigate pragmatic, convenient and time-saving physical activity and exercise interventions that will maximise overall health benefits, and that are feasible in engaging both healthy and clinical populations.

### High intensity interval training

High intensity interval training (HIIT), has received much recent attention in health literature as a time-saving, effective exercise modality for cardiometabolic health [37]. HIIT is characterised by bouts of vigorous activity separated by short rest intervals. These vigorous intensity exercise bouts typically require maintaining intensity thresholds of at least 85% of an individual’s maximum heart rate (HR), followed by active or passive rest at 65% maximum HR [37]. Although there are a myriad of protocols used, most evidence suggests that HIIT is equally if not more beneficial for cardiometabolic health compared to moderate intensity continuous training (MICT) [38]. Therefore, HIIT may offer an effective solution to people who struggle to maintain adequate levels of physical activity. The most commonly observed primary outcome measure in HIIT studies is a change in peak oxygen consumption (VO_2_peak) as an indirect measure of improvement in cardiovascular disease risk [39]. Various other improvements in cardiometabolic health markers are also observed in trials investigating HIIT in adults with overweight/obesity, including reductions in systolic and diastolic blood pressure [40, 41], reversal of dyslipidemia [42, 43], improvements in insulin resistance, glycated haemoglobin (HbA1c) and fasting blood glucose concentrations [43–45]. The improvements in cardiometabolic risk factors are observed following both short term (< 12 weeks) and long term (> 12 weeks) participation in HIIT interventions despite no significant change in body composition [40].

### Feasibility of HIIT interventions

To date, the vast majority of studies investigating the efficacy of HIIT in adults with overweight or obesity have used supervised, lab-based running and cycling protocols [40, 46, 47]. However, HIIT may be performed through various movements and is not limited to running or cycling. Other own-body weight exercises for use in HIIT have gained popularity and are easily conducted in the comfort of one’s home. Whether home-based HIIT activity produces similar cardiometabolic benefits to the classic running and cycling protocols needs investigation because understanding the feasibility of engagement in physical activity outside of research and clinic settings is important for understanding how to sustain health benefits. To our knowledge, only one recent study examined the effects of an unsupervised, home-based HIIT programme on body mass over 12 months in overweight adults [48]. Although overall long-term adherence to the intervention was significantly low (23% of participants fully adherent), those participants who adhered to the programme showed greater reductions in body mass compared to non-adherent individuals [48], with adherent HIIT individuals performing the exercises for between 21 and 24 min per week. It is currently unknown whether a home-based HIIT can produce improvements in risk factors for cardiovascular and metabolic diseases.

The difficulty in prescribing an adequate dose of HIIT for loss of fat mass is largely due to the variability in protocols used in interventions [49, 50]. Cowan et al. [51] have shown in women with abdominal obesity that continuous, aerobic exercise for 24 weeks resulted in a reduction in total and abdominal adipose tissue independent of the amount or intensity of exercise. Women in a low-intensity, low-volume group who exercised for 30 min per session showed similar reductions in adipose tissue compared to the high-volume, high-intensity group (40 min/session) and the high-volume, low-intensity (almost 60 min/session) group [51]. Some HIIT studies exceed the recommended guidelines for weekly vigorous physical activity, an amount of time which appears to be difficult to achieve in many populations [3, 26]. If sustained participation in any exercise is a primary factor in determining benefits to cardiovascular health, more studies of the feasibility of participation in low volume HIIT are needed. In addition, more randomized controlled trials using a healthy group comparator should be done to determine whether there are differences in the effects of HIIT between people with chronic disorders affecting cardiometabolic health and people free from chronic disorders [40]. These studies may guide further investigations into understanding the physiological mechanisms underlying the benefits previously seen in HIIT trials.

Globally, public health interventions to decrease the prevalence of high body mass are failing to yield the desired outcomes in individual countries [22, 52]. Alternative and feasible exercise interventions that lower the risk of developing NCDs are important to investigate in women, who may often face multiple barriers to regular exercise participation. This paper describes the protocol for a randomised controlled trial to primarily assess effects of a 14-week high-intensity low-volume interval training intervention on the cardiorespiratory fitness of women with overweight/obesity and women of normal body mass. The study secondly aims to determine the effect of the intervention on body composition and cardiometabolic health as well as the feasibility of the intervention in the groups of women.

## Methods/design

### Study objectives

This randomised controlled trial will compare the effects of a 14-week low-volume high-intensity interval training intervention on cardiorespiratory fitness, body composition and cardiometabolic health in women of normal body mass and women with overweight/obesity. In addition, adherence to and drop-out rate of the intervention will be measured to determine feasibility. We hypothesise that at the end of the 14-week intervention, women with overweight/obesity performing HIIT will have significant changes in their cardiorespiratory fitness and cardiometabolic health regardless of a change in body composition. We also expect that a low-volume HIIT intervention will be feasible in this cohort of women.

### Study design

This study will be a randomized controlled trial (Fig. 1), where equal numbers of participants (normal and high BMI) will be assigned to either a HIIT group (HIIT) or a control (CON) group. The study has been designed using the SPIRIT guidelines (Fig. 2 and Additional file 1). The reporting of the trial will be guided by the CONSORT statement for clinical trials. Women in the HIIT group will complete a home-based high intensity exercise program for 14 weeks. The control group will be asked to maintain their current activity and dietary behaviours. Physiological measurements of cardiorespiratory fitness, body composition and cardiometabolic health will be done at baseline and on completion of the intervention at the 14th week. Habitual activity behaviours will be determined objectively using accelerometers for a week prior to the start of the intervention and for a week following the intervention. During the intervention, monitoring of and adherence to the HIIT protocol will also be assessed with accelerometers and an exercise diary. The study has been approved by the University of the Witwatersrand Human Research Ethics Committee (protocol number: M180253). Informed consent will be obtained from all participants prior to entry into the study. The trial has been registered on the Pan African Clinical Trial Registry (www.pactr.org - id no: PACTR201806003434299).

**Fig. 1 Fig1:**
[figure not shown]
Flow of participants through the study

**Fig. 2 Fig2:**
[figure not shown]
SPIRIT schedule of enrolment, intervention and assessments for the duration of the study

### Study site

The study measures will be conducted at the Movement Physiology Research Laboratory in the School of Physiology in Johannesburg, South Africa. The laboratory is situated in Parktown in the Faculty of Health Sciences, University of the Witwatersrand. Participants will conduct the 14-week intervention outside of the laboratory setting.

### Recruitment of participants

Volunteers will be recruited from the academic community of the University as well as from the surrounding central business district. Study advertising will be placed on the online University newsletter, social media platforms such as Facebook, through direct invitation by the research team via their teaching roles and posters with study information will be displayed throughout the University’s faculties. The expected time frame for recruitment of participants is anticipated to take 18–24 months. Eligible volunteers will be enrolled into the study as and when they volunteer. Participants will be compensated for their costs incurred travelling to the laboratory for assessments. Recruitment of participants started on 1st July 2018 and is ongoing, and data collection is in progress.

### Study participants/eligibility criteria

Women between the ages of 18 and 40 years will be invited to participate in the study. Women will be included if they have a BMI between 20 and 35 kg/m^2^ (normal to obese BMI categories) and are free from injury and/or known clinical conditions which would exclude them from partaking in exercise as assessed using the physical activity readiness questionnaire (PAR-Q). Known clinical conditions include family history of sudden death, uncontrolled hypertension, type I or type II diabetes and cardiovascular disease. No pre-requisite training background is required however participants will be excluded from the study if they report engaging in competitive exercise or take part in a structured exercise programme that has been prescribed by a physical trainer or other health-related exercise professional. Exclusion criteria are also women with a BMI < 20 kg/m^2^ or > 35 kg/m^2^, and if they report any diagnosed underlying cardiometabolic condition including hypertension, diabetes or cardiovascular disease. All volunteers will be informed verbally and in writing of the procedures of the study before signing an informed consent form and completing screening questionnaires. Participants will be asked to maintain their habitual diet throughout the study.

#### Sample size determination

Based on a small effect size of 0.20 (Cohen’s f) for an improvement in relative VO_2_peak after HIIT versus no HIIT [42], performing a priori sample size calculation for a repeated measures analysis of variance with an expected correlation of 0.50 between measurements, alpha of 0.05 and 85% power of detection, a total sample size of 60 women will be required (G*Power, version 3.1.9.2). The sample size will be doubled to account for further planned analysis of secondary outcomes in sub-groups of normal and high BMI women (HIIT normal BMI, HIIT high BMI, CON normal BMI, CON high BMI). The target sample size will be therefore be 120 women exclusive of drop outs.

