### Outcome measures

The primary outcome of the trial is a change in cardiorespiratory fitness after the 14-week HIIT intervention. Secondary outcomes are changes in body composition, cardiovascular health and metabolic biomarkers of health, as well as measures of feasibility and physical activity and sedentary behaviour levels. Both primary and secondary outcomes will be measured before and after the 14-week intervention (Fig. 2).

Table 1 summarises the outcome measures to be made and the time points at which they will be measured during the study.

**Table 1 Tab1:** Indication of physiological variables measured and timepoints of each measurement

Variable	Timepoints measured
*Primary outcome*	
Peak VO_2_, HR at peak VO_2_, HR at 65 and 85% peak VO_2_	Baseline, post-intervention
*Secondary outcomes*	
Anthropometry	
Skinfolds	Baseline, post-intervention
Body mass and waist:hip	Baseline, every 4 weeks during intervention, post-intervention
Brachial blood pressure	Baseline, post-intervention
Central blood pressure and arterial stiffness	Baseline, post-intervention
Echocardiography	Baseline, post-intervention
Biomarkers of metabolic and cardiovascular health	Baseline, post-intervention
Feasibility (adherence and dropout rate)	Baseline, every 4 weeks during intervention, post-intervention
Accelerometry	Baseline, every 4 weeks during intervention, post-intervention

*VO*_*2*_*peak* Peak oxygen consumption, *HR* Heart rate

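### The sample size section calls Cohen's f = 0.20 small, but in the calculation that yields 60 women it is a 0.80 SD between-arm difference in change

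*Protocol article*

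**What the plan says.** Under Sample size determination, the protocol article describes its planning effect this way: "Based on a small effect size of 0.20" (Cohen's f), "for an improvement in relative VO_2_peak after HIIT versus no HIIT". The method is an "a priori sample size calculation for a repeated measures analysis of variance" run in G*Power, with an "expected correlation of 0.50 between measurements" and "alpha of 0.05 and 85% power of detection". The result is 60 women in total. The section does not say which effect of the ANOVA (time, group, or group by time) was sized. It gives no expected VO2peak difference in ml/min/kg and no SD.

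The 60 is then doubled to 120. The reason given is secondary-outcome analysis in the BMI sub-groups, not a wish to detect a smaller primary effect. Under Outcome measures: "Both primary and secondary outcomes will be measured before and after the 14-week intervention". The primary analysis therefore has two timepoints. Study design and Randomisation set two arms of equal planned size, with 30 women per arm in each BMI stratum.

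**The concern.** Cohen's f in a repeated-measures ANOVA is not on the same footing as a standardised difference between two groups. What a given f means depends on which effect is tested and how the software defines it. A reader who sees 60 women and 85% power for a small effect will conclude that the trial is sensitive to modest changes in fitness. Sixty women, 30 per arm, cannot have that power for a small between-arm difference in change when the correlation is 0.50, so either the number or the label needs explaining.

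What is at stake is the reading of the result. If the label is taken at face value, a non-significant primary comparison would seem to rule out even a small benefit of home-based HIIT. The design does not support that inference.

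**Working it through.** **Inputs, all from the protocol article.** f = 0.20, correlation rho = 0.50, alpha = 0.05 and power 85% (Sample size determination); m = 2 measurements (Outcome measures); k = 2 equal arms (Study design).

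**Step 1: reproduce the 60.** For the group-by-time interaction under G*Power's default definition, the noncentrality is

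lambda = f² × N × m / (1 − rho) = 0.04 × N × 2 / 0.5 = 0.16N, with 1 and N − 2 degrees of freedom.

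- N = 58: power 0.849.
- N = 60: lambda = 9.6, power 0.861.

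Sixty is the smallest even total that reaches 85%, so the stated figure reproduces exactly.

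**Step 2: rule out other readings with f = 0.20.**

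| Reading | Total N for 85% power |
|---|---|
| Group by time, 2 arms | 60 |
| Time (within-factor) | 60 |
| Group (between-factor), 2 arms | 172 |
| Group by time, 4 groups | 84 |
| Group by time, 2 arms, lambda = f²N | 228 |

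The time effect also gives 60, but it does not compare HIIT with no HIIT. Only the two-arm interaction fits both the stated contrast and the stated number.

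**Step 3: convert f to a difference.** Let delta be the difference between arms in mean change and sigma the SD of a single measurement. In a 2 × 2 layout each interaction cell effect is ± delta/4, so

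f = delta / (4 sigma), and delta = 4 × 0.20 × sigma = 0.80 sigma.

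The SD of change is sigma × √(2(1 − rho)) = sigma × √(2 × 0.5) = sigma. At the stated correlation the target is therefore also 0.80 SD of change.

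**Step 4: cross-check.** A two-sample t-test on change with n = N/2 per arm has squared noncentrality delta² × n / (2 × SD of change²). Here that is 0.64 × 30 / 2 = 9.6, the same as in Step 1. Its power at d = 0.80 with 30 per arm is 0.861, and a simulation of 40,000 trials gives 0.860.

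**Step 5: sensitivity at 60 and 120 women** (two-sided t-test on change, rho = 0.50).

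| Difference in change | Power, N = 60 | Power, N = 120 | Total N for 85% power |
|---|---|---|---|
| 0.2 SD | 12% | 19% | 900 |
| 0.4 SD | 33% | 58% | 228 |
| 0.5 SD | 48% | 78% | 146 |
| 0.8 SD | 86% | 99% | 60 |

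The 0.4 SD row is what f = 0.20 means in an ordinary two-group comparison (d = 2f). The difference detectable with 85% power is 0.79 SD with 30 per arm (one BMI stratum) and 0.55 SD with 60 per arm (the planned overall comparison).

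**Step 6: natural units.** The article gives no SD. Assuming 5 to 7 ml/min/kg, for illustration only, and rho = 0.50:

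- 0.80 SD is 0.80 × 5 = 4.0 to 0.80 × 7 = 5.6 ml/min/kg.
- 0.55 SD is 0.55 × 5 ≈ 2.8 to 0.55 × 7 ≈ 3.9 ml/min/kg.

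**The case against.** **The calculation is right and its inputs are disclosed.** This stands. The metric, correlation, alpha, power and software are all given, and 60 follows from them. On the f scale, 0.20 also lies below the conventional medium value of 0.25. But that convention does not carry over to this use of f, where the same 0.20 corresponds to d = 0.80. A reader might infer that 60 is a miscalculation. It is not.

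**The trial will enrol 120, not 60.** This also stands. A reader might infer that the trial as planned protects only against a large effect. With 60 per arm the overall comparison has 85% power for about 0.55 SD, which is moderate. The 0.8 SD figure belongs to the calculated 60 and, nearly, to each BMI stratum. Even so, 0.55 SD is not small.

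**Adherence.** A reader might infer that 0.8 SD is optimistic because, in the one earlier home-based study, "overall long-term adherence to the intervention was significantly low (23% of participants fully adherent". The documents do not support this. That programme ran for 12 months and was assessed on body mass, whereas this one runs for 14 weeks and is judged on VO2peak. With no expected difference or SD given, whether 0.8 SD is realistic cannot be settled here.

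**Dropout.** A reader might discount the 120 for losses. The section states 120 as not counting dropouts, and no loss rate is given, so a reduced-completer scenario has no basis in the document.

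**Dependence on the correlation and the model.** In single-measurement SD units, f = 0.20 is 0.80 whatever the correlation. The difference detectable with 120 women is not fixed: 0.552 × √(2(1 − rho)) gives about 0.65 sigma at rho = 0.3 and 0.43 sigma at rho = 0.7. The planned covariates, age and baseline activity, are not in the change-score calculation either.

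**Omission from a condensed article.** Not stating the sensitivity at 120 would be no finding by itself. The point is the word that is stated, and that word is wrong for the test used. The article does not itself say that a null result would exclude small benefits, and it commits to reporting effect sizes.

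**Conclusion.** The point holds as an error of label and implied sensitivity, not of arithmetic. The effect called small is a 0.80 SD between-arm difference in change, which the usual d convention (0.2 small, 0.5 medium, 0.8 large) calls large. At the planned 120 women, power is 19% for 0.2 SD and 58% for 0.4 SD, so a null primary result would leave differences of that size open. The stratum-level sensitivity of about 0.79 SD matters because the hypothesis in Study objectives is framed for women with overweight or obesity.

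The conclusion assumes that the interaction was the effect sized. The article does not say so, but no other reading checked fits both the contrast and the 60. The power figures assume correlation 0.50 and a comparison of change scores. The ml/min/kg figures also rest on an assumed SD.

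**What to change.** In Sample size determination, delete the word small and name the group-by-time interaction as the effect tested. Restate the basis along these lines:

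> Sixty women give 86% power for a 0.8 SD difference between HIIT and CON in change in relative VO2peak (correlation 0.5); 120 women give 85% power for 0.55 SD.

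Add the ml/min/kg equivalent with the SD assumed, and note that each BMI stratum has 85% power for about 0.79 SD. When the trial is reported, give the confidence interval for the difference in change and do not read a null result as excluding smaller effects.

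The cost is a change of wording and a less favourable stated sensitivity. Enrolment, allocation, outcome and analysis stay as they are.
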